**Methods/Design:**

A double blind placebo-controlled multi-center randomized clinical trial will be performed in 30 children with dystonic cerebral palsy. Patients aged between 4 and 25 years old with a confirmed diagnosis of dystonic cerebral palsy, Gross Motor Functioning Classification System level IV or V, with lesions in the cerebral white matter, basal ganglia or central cortex and who are eligible for intrathecal baclofen treatment will be included. Group A will receive three months of continuous intrathecal baclofen treatment and group B will receive three months of placebo treatment, both via an implanted pump. After this three month period, all patients will receive intrathecal baclofen treatment, with a follow-up after nine months. The primary outcome measurement will be the effect on activities of and participation in daily life measured by Goal Attainment Scaling. Secondary outcome measurements on the level of body functions include dystonia, spasticity, pain, comfort and sleep-related breathing disorders. Side effects will be monitored and we will study whether patient characteristics influence outcome.

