### Objectives

The primary objective of the present study is to show whether ITB treatment improves activities of and participation in daily life (for example dressing, transfer, sitting in a wheelchair, hygienic care, speech) in dystonic CP patients. Certain patient characteristics, such as the location and severity of MRI lesions and Gross Motor Functioning Classification Score (GMFCS) level, might influence the effects of ITB treatment in patients with dystonic CP. Therefore, we will study whether individual patient characteristics (GMFCS, gender, age, MRI findings and co-medication) influence outcome and could be used in determining the indication for ITB in future patients. A secondary objective is to provide evidence for the effect of ITB on the level of body functions. The relevant clinical questions to be addressed are: 1. Does ITB decrease dystonia? 2. Does ITB decrease spasticity in dystonic patients? 3. Does ITB decrease pain? 4. Does ITB increase comfort? 5. Does ITB influence screening results of sleep-related breathing disorders? 6. What are the side effects of ITB?

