### Primary outcome measure

The primary outcome measurement will be on the level of activities and participation. Goal attainment scaling (GAS) will be used to measure the effect of ITB treatment. Using GAS, achievement of individual set goals can be quantified. This method was introduced for assessing outcomes in mental health settings and has been used in many other areas
[13,14]. Each subject has their own outcome measure, but statistical analysis is possible because they are scored in a standardized way. This procedure is time-consuming and requires about 45 minutes per child
[15,16]. However, after the scale is constructed, it should be possible to score a patient within 10 minutes
[17].

The procedure includes the following aspects:

1) Identification of goals:

Three main problems of daily care and function will be determined by caregivers. Goals will be set for these problems with the help of the team to ensure that goals are achievable. Goals should be specific, measurable, attainable, realistic and timely (SMART)
[13,14]. The target activity, specific support and time period should be specified and performance should be quantified using distance, frequency or time taken to accomplish a task
[14].

2) Weighing of goals:

Some goals will be more important for subjects than others
[13]. Goals can be assigned a weighing score by caregivers and a difficulty score by the team
[14]. We chose not to assign weighing scores since the weighted and unweighted scores are closely correlated
[18]. A value of 1 is applied to ‘weight’ in the formula described below.

3) Definition of expected outcomes:

Several approaches are described in literature, varying from 5 to 7 point scales
[14,15]. We will use a 6 point scale ranging from -3 to +2, since we wish to include both the possibility of partially achieving the set goal and to avoid a bottoming effect. Baseline scores will be allocated as -2. If the subject achieves the expected level, this is scored as 0. If a subject does not achieve the expected level but shows improvement, this is scored as -1. If they achieve more than the expected outcome, this is scored as +1 for somewhat more and +2 for much more. We chose to add a score of -3 in case of deterioration. Each goal level will be defined by the investigator so as to be as objective and observable as possible
[13].

4) Scoring goal attainment:

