#### Univariate analysis

The GAS t-scores, BAD score, SPAT score and EMG activity in the placebo and ITB group will be compared using an independent samples t-test. If the assumption of normality appears not to be valid, the non-parametric Mann–Whitney test will instead be used. A p-value of 0.05 is considered statistically significant for this primary analysis. To assess within-group changes in means between follow-up times and baseline GAS t-scores, BAD score, DIS score, SPAT score and EMG activity, a paired t-test or non-parametric Wilcoxon test will be used (depending on whether the normality assumption is valid). In these analyses, a p-value of 0.05 is considered to be statistically significant.

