#### Multivariate analysis

A multivariate analysis will be used to determine the effect of ITB treatment (primary: functional outcome; secondary: dystonia and the interaction with GMFCS, MACS, MRI classification and use of co-medication).

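### The Dyskinesia Impairment Scale (DIS) is listed for before-after testing but left out of the ITB-versus-placebo comparison

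*Protocol article*

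**What the plan says.** All references are to the protocol article.

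- **Univariate analysis, between groups.** "The GAS t-scores, BAD score, SPAT score and EMG activity in the placebo and ITB group will be compared using an independent samples t-test", with Mann–Whitney as the fallback. The 0.05 level is attached to this comparison, which the text calls primary.
- **Univariate analysis, within groups.** The next analysis is introduced by "To assess within-group changes in means between follow-up times and baseline GAS t-scores, BAD score, DIS score, SPAT score and EMG activity". It uses a paired t-test or Wilcoxon test, again with 0.05 as the threshold for significance.
- **Dystonia (secondary outcome measures).** Blinded raters score videos on both BAD and DIS. DIS is used in addition to BAD, and the authors remark that BAD has high interrater variability.
- **Descriptive statistics.** DIS is absent from the baseline table but present in the follow-up table by group.
- **Multivariate analysis.** The ITB effect is studied on functional outcome and, in second place, "secondary: dystonia and the interaction with GMFCS, MACS, MRI classification and use of co-medication". No dystonia instrument is named.
- **Objectives and abstract.** The secondary questions include "3. Does ITB decrease pain? 4. Does ITB increase comfort? 5. Does ITB influence screening results of sleep-related breathing disorders". The abstract agrees: "Secondary outcome measurements on the level of body functions include dystonia, spasticity, pain, comfort and sleep-related breathing disorders". None of the three statistical subsections mentions pain, comfort, the sleep-breathing questionnaire or the H/M ratio.

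**The concern.** The trial has a placebo arm so that changes under ITB can be judged against changes without it. For DIS the printed plan does not use that arm in any named test. It compares follow-up with baseline inside each group and attaches a significance threshold to the result.

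A before-after change mixes any drug effect with placebo response and regression to the mean. Patients are selected because their movement disorder is severe, so some drift towards lower scores would be unsurprising even without an active drug.

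What is at stake is a secondary dystonia claim. A report that follows the text could present a significant fall in DIS under ITB with no randomised comparison beside it. DIS was added next to a scale whose rater variability the authors acknowledge, so readers may give it real weight.

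**Working it through.** **1. The plan's own figure.** The sample size section anticipates GAS changes of 0 (SD 8.5) on placebo and 12.5 (SD 10) on ITB, with 90% power and two-sided 5%.

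- Pooled SD = √((8.5² + 10²)/2) = √86.125 = 9.28
- Standardised difference = 12.5/9.28 = 1.347
- Noncentral t, 2n − 2 degrees of freedom, noncentrality 1.347 × √(n/2): power is 0.883 at n = 12 and 0.909 at n = 13.

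The stated 13 per group is reproduced. It depends on GAS alone, so nothing below changes it.

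**2. Outcomes against printed analyses.**

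| Outcome | Between-group test | Within-group test | Follow-up table by group |
|---|---|---|---|
| GAS | yes | yes | yes |
| BAD | yes | yes | yes |
| SPAT | yes | yes | yes |
| EMG | yes | yes | yes |
| DIS | **no** | yes | yes |
| VAS pain, VAS comfort | no | no | no |
| Sleep-breathing questionnaire | no | no | no |
| H/M ratio | no | no | no |

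DIS is the only outcome that is in one test list and missing from the other. Dystonia as a question still has between-group tests (BAD, and EMG as a measure of the underlying muscle activity). Spasticity still has SPAT.

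**3. What a before-after test can show.** Suppose ITB has no effect on DIS, but scores change for other reasons by m standard deviations of the change score. The article gives no value for m, so 0.25 to 0.75 is an assumption. The chance of a significant paired t-test at two-sided 0.05 comes from the noncentral t with n − 1 degrees of freedom and noncentrality m√n.

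| m | n = 13: m√n | n = 13: chance | n = 15: m√n | n = 15: chance |
|---|---|---|---|---|
| 0 | 0 | 5% | 0 | 5% |
| 0.25 | 0.90 | 13% | 0.97 | 15% |
| 0.50 | 1.80 | 38% | 1.94 | 44% |
| 0.75 | 2.70 | 70% | 2.90 | 77% |

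In a between-group test, a change common to both arms cancels and the error rate stays at 5%.

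Setting the two arms' paired tests side by side does not solve this. With m = 0.5 in both arms and n = 15, the chance that ITB is significant and placebo is not is 0.438 × (1 − 0.438) = 0.25, although the arms do not differ.

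**4. What the added comparison could detect.** A two-sided 5% t-test at 15 per group detects a standardised difference of 1.06 with 80% power and 1.23 with 90%. At 13 per group the values are 1.15 and 1.33. Only large differences are likely to reach significance, so the estimate and its interval will matter more than the p-value.

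**The case against.** The best counter-argument is that this is a drafting slip in a condensed article. DIS is also missing from the baseline table yet present at follow-up, which looks like careless listing. The Intervention section says in general terms that the groups will be compared at three months, follow-up DIS is tabulated by group, and the multivariate analysis of dystonia could include DIS. All of that is fair, and it argues against reading the omission as a decision to assess DIS without a control. It does not remove the mismatch. The general statement names no outcome, a table is not a test, and the multivariate sentence names no instrument.

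Three stronger readings are tempting, and the document does not support them.

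- **Pain, comfort and sleep breathing will get no randomised answer.** A reader might infer this because no list mentions them. But the list is not said to be exhaustive, and an article commonly leaves secondary tests to a full protocol or analysis plan. The same holds for the H/M ratio, whose measurement schedule is not given in the text. Adding them is sensible tidying, but their absence is not an error in itself.
- **Four outcomes share the primary test, so the false-positive rate is inflated.** The primary label is loosely placed. However, the abstract, the sample size section and the Primary outcome measure section all make GAS the primary outcome. Nowhere does success on any one of the four count as a positive trial.
- **The paired GAS test is invalid because baseline is fixed** ("Baseline scores will be allocated as -2"). It is then a valid one-sample test of change, and GAS has its between-group test anyway.

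It is also fair that at twelve months every subject is on ITB after nine further months of open treatment. No concurrent placebo group remains then, so within-group change is the natural summary.

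**Conclusion.** The point holds for DIS. Two explicit lists in one paragraph disagree, and followed literally they give a blinded dystonia scale a significance test against its own baseline and no named test against placebo. Under the assumed non-specific change of 0.25 to 0.75 SD, that paired test would be significant in 15% to 77% of trials at 15 per arm (13% to 70% at 13) with no drug effect. These percentages illustrate the weakness of the design; they do not predict what DIS will do.

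The consequence is confined to secondary evidence. The dystonia and spasticity questions keep randomised comparisons, and the primary GAS analysis and the 13 per group stand. The uncovered outcomes and the loose primary label are wording to settle in the same edit. An analysis plan that is not shown may already settle them.

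**What to change.** Revise the Univariate analysis paragraph as follows.

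1. Add DIS to the between-group comparison, and state that this comparison is made at three months.
2. In the same sentence, name the other stated secondary outcomes: VAS pain, VAS comfort, sleep-breathing screening, and the H/M ratio if it is measured. Give each a test suited to its scale, for example Fisher's exact test for a positive sleep-breathing screen.
3. Restrict the primary label to the GAS T-score at three months. Call the remaining comparisons secondary and supportive.
4. For the blinded period, report within-group changes as estimates with confidence intervals. Say that they are descriptive and not evidence of an ITB effect.

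The cost is analysis wording only, with no change to the sample size. The price is more secondary tests: BAD, SPAT and EMG become seven outcomes, or eight with the H/M ratio. They should be read as supportive, with intervals given for each.

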### Intervention

Included subjects will be randomized in two groups. Group 1 will receive placebo treatment via an implanted micro-infusion pump for three months. Group 2 will receive ITB treatment via an implanted micro-infusion pump for three months. In our opinion, it is unethical to continue placebo treatment for more than three months. If interim analysis shows that subjects in one of the groups have significant disadvantages compared to the other group, the study will be prematurely terminated. On the other hand, we know from experience that dosages for some patients are still being modified three months after starting treatment. As a consequence, the effect of treatment in these patients may not yet be optimal, which may then result in no detectable effect of ITB treatment at that point. We will try to reduce this possible effect through frequent dose modification. Patients will be seen once or twice weekly to increase their dosage, until either a stable dosage or a maximal dosage of 800 μg/day is achieved.

Subjects will be assessed at three months and the effect of treatment in the two groups compared. Since determining the most beneficial pump setting can take more than three months and because the initial effect may recede in some cases, all subjects will receive subsequent ITB treatment for nine months. Following this 9 month period, clinical evaluation will be performed in order to determine long-term effects (see Figure 
1. Flow Chart of Subjects).

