For each assessment, one assessor will make a standardized video recording during trials for each of the three functional ability goals. The recording procedure will be identical for all measurements. Another assessor, blinded for group allocation, will rate the subject’s performance from the video recordings. Although the GAS only simulates the subject’s own functional setting, parents were convinced that the outcome of scaling was representative of their own setting
[19].

Goal attainment scores will be recorded at baseline, after three months of blinded treatment and after nine months of ITB treatment. Goal attainment change scores will be determined by subtracting the baseline score from the outcome score. Subjects who achieve a GAS T-score >50 achieved their goals
[8]. Clinical relevance will be defined as an improvement of at least two points in at least one of the three goals
[19].

A single aggregated score (T-score) can be produced by a standardized mathematical formula: Overall GAS = 50+ 10∑(w_i_x_i_) / √((1-ρ) ∑w_i_^2^ + ρ(∑w_i_)^2^); W_i_ is the weight assigned to the goal, x_i_ is the numerical value achieved (between -3 and +2), ρ (rho) is the expected correlation of the goal scales, which is normally 0.3
[13,14].

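### Uncontrolled within-arm changes are declared significant at 0.05 on five outcomes, with the randomised month-3 point not excluded; for DIS this is the only test listed

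*Protocol article*

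**What the plan says.** The Univariate analysis section of the protocol article sets out two families of tests.

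- **Between groups.** "The GAS t-scores, BAD score, SPAT score and EMG activity in the placebo and ITB group will be compared using an independent samples t-test", with Mann–Whitney as the fallback. The threshold is 0.05 and the section calls this the primary analysis. DIS is not in the list.
- **Within groups.** The stated purpose is: "To assess within-group changes in means between follow-up times and baseline GAS t-scores, BAD score, DIS score, SPAT score and EMG activity". Depending on normality, the test is either Wilcoxon's or the paired t-test. The section then states: "In these analyses, a p-value of 0.05 is considered to be statistically significant". DIS is in this list.

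The within-group rule is not restricted to the open-label phase.

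The Intervention section makes month 3 the randomised time point: "Subjects will be assessed at three months and the effect of treatment in the two groups compared". After that all subjects receive ITB for nine months, so month 12 has no placebo comparison. For GAS the assessment times are explicit: "Goal attainment scores will be recorded at baseline, after three months of blinded treatment and after nine months of ITB treatment". The Objectives section adds: "A secondary objective is to provide evidence for the effect of ITB on the level of body functions".

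**The concern.** At month 3 the trial has a concurrent placebo arm, obtained at the price of pump implantation and three months of placebo infusion. A within-arm test at that point discards it. The test responds to placebo response, regression to the mean and natural change as readily as to the drug.

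GAS is especially exposed. Every goal starts at -2 on a scale from -3 to +2, so each subject has one level below the starting point and four above it. The goals are set on the child's three main problems. Because the baseline is a constant, the paired GAS test is in effect a one-sample test of follow-up against a fixed value near the bottom of the scale.

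At stake is what may be reported. Under the stated rule, a significant ITB-arm improvement at month 3 can appear beside a null randomised comparison. For DIS, one of the two dystonia rating scales, the uncontrolled test is the only one the section lists.

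**Working it through.** **1. The plan's own figure.** The Sample size calculation gives a difference of 12.5 (12.5 against 0), SDs of 10 and 8.5, a two-sided 5% independent samples t-test, 90% power and 13 per group. The root-mean-square SD is √((8.5² + 10²)/2) = 9.28. From the noncentral t distribution, power is 88.3% at 12 per group and 90.9% at 13, so 13 is reproduced. At the 15 per group to be enrolled, power is 94.5%. The primary design is sound.

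**2. Size of one GAS step.** With three goals, weights of 1 and ρ = 0.3, the denominator in the Primary outcome measure section is √(0.7 × 3 + 0.3 × 9) = √4.8 = 2.19. One level on one goal is therefore 10/2.19 = 4.6 T-points. The baseline with all goals at -2 is 50 − 60/2.19 = 22.6.

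**3. Equal shift in both arms, no drug effect.** The shift is an assumption; the protocol anticipates a placebo change of 0. Inputs are n = 15 per arm and the protocol's SDs of change (ITB 10, placebo 8.5). Each arm's test has noncentrality (shift/SD) × √15 on 14 degrees of freedom. Let *a* and *b* be the probabilities of significance in the ITB and placebo arms. Then ITB alone is *a*(1 − *b*), and disagreement is *a*(1 − *b*) + *b*(1 − *a*).

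| Assumed shift (T-points) | ITB arm significant (*a*) | Placebo arm significant (*b*) | ITB alone | Arms disagree |
|---|---|---|---|---|
| 0 | 5% | 5% | 5% | 10% |
| 2 | 11% | 14% | 10% | 22% |
| 4.6 | 38% | 49% | 19% | 50% |
| 6 | 58% | 72% | 16% | 46% |

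For 4.6 points: 0.377 × (1 − 0.491) = 0.192, and 0.192 + 0.491 × (1 − 0.377) = 0.498. The between-group test is unaffected by a shift common to both arms; simulated with these unequal SDs it rejects in 5.0% of trials.

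**4. Chance alone, no true change.** Five outcomes in two arms give 10 tests at month 3. Over two follow-ups the count is 5 × 2 × 2 = 20. If the tests are independent, the chance of at least one p < 0.05 is 1 − 0.95¹⁰ = 40% for the 10 and 1 − 0.95²⁰ = 64% for the 20. The documents give no correlations, so these were varied in simulations of paired t-tests, with 0.5 or 0.7 assumed between follow-ups:

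| Assumed correlation between outcomes | At least one of 10 (month 3) | At least one of 20 |
|---|---|---|
| 0 | 40% | 58–62% |
| 0.5 | 33–34% | 51–55% |
| 0.9 | 20% | 32–34% |

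These rates are two-sided and count either arm. The narrower event of a false *improvement* in the *ITB arm* at month 3 involves five tests in one direction. It is at most about 1 − 0.975⁵ = 12%, and about 5 to 10% with outcome correlations from 0.9 down to 0.5.

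**The case against.** The strongest reply is that the protocol already ranks its analyses. The between-group test comes first and is called primary, the sample size is built on it, and the Intervention section judges the three-month effect by comparing groups. That stands. A reader might infer that the plan puts the within-arm tests on an equal footing or leaves their order open; the text does not support this. Reading a within-arm result as a verdict on ITB is a reporting risk, not a decision rule in the protocol. Nor does the Objectives section say that evidence on body functions will come from within-arm tests: BAD, SPAT and EMG each have a between-group test.

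A reader might also infer that about half of such trials would show a false significant change at month 3. That figure belongs to all 20 tests at an assumed correlation of about 0.5. The month-3 rate is 20 to 40%, and a chance ITB-arm improvement is rarer still.

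Two further limits stand. Two follow-ups are explicit only for GAS; for the other outcomes they are read from the plural wording, and the flow chart is not available here. At month 12 both arms have received ITB, so a change may be real. The difficulty there is attribution, which a family-wise error rate does not measure.

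It can also be said that labels for secondary tests belong in an analysis plan that is not shown. This does not dispose of the point, because the article does not leave the matter open: it states a significance threshold for these tests, and it lists DIS only among them.

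**Conclusion.** The point holds as a fault in a secondary analysis rule, not in the primary inference. The plan attaches a 0.05 significance label to uncontrolled changes on five outcomes, does not exclude the time point at which a randomised comparison exists, and gives DIS no listed alternative.

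The main argument is bias rather than multiplicity. With an equal, drug-free improvement of 4.6 T-points in both arms, the ITB arm is significant in about 38% of trials and ITB alone in about 19%. These figures rest on the assumed shift, the protocol's SDs and 15 per arm, and they shrink towards 5% if the anticipated placebo change of 0 is correct. The chance-alone rates, 20 to 40% at month 3 and about one third to two thirds over 20 tests, rest on assumed correlations, no true change in either arm and, for the 20, two follow-ups for every outcome.

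**What to change.** In the Univariate analysis section:

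1. Add DIS to the between-group comparison at month 3, so that removing its within-arm test does not leave it without any test.
2. Replace the month-3 within-arm significance tests by the mean change per arm with a 95% confidence interval, and state that month-3 conclusions on ITB rest only on the between-group comparison.
3. Report month-12 within-arm changes as descriptive or exploratory estimates with 95% confidence intervals, not as evidence of an ITB effect. A multiplicity correction is no substitute: it limits chance error but does not supply a control.

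The cost is a few sentences, with no new patients, data or procedures. Fewer results may be called significant. The primary alpha, the power (90.9% at 13 and 94.5% at 15 per group) and the sample size stay as they are.
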